### Intervention

#### The Treatment and Education Approach for Childhood-Onset Lupus (TEACH) Intervention

The TEACH intervention is a brief, remotely delivered intervention individualized to common cSLE symptoms and developed with patient/caregiver co-investigative feedback. It draws primarily from CBT strategies known to be effective in addressing fatigue [7], mood [8, 9], and pain symptoms [10, 11], and incorporates mindfulness meditation. Remotely delivered psychological therapy is considered to be as effective and more accessible to patients with co-morbid mood concerns than conventional in-person approaches [40].

TEACH was originally developed by the PI with her research team at Cincinnati Children’s Hospital Medical Center [18], and was modified from established CBT protocols for fatigue [41] and pain [42], with additional refinements made to address mood symptoms, developmental level (e.g., separate protocols for adolescents versus young adults), and other issues affecting those with cSLE (e.g., medication adherence). The research team partnered with five patients/caregiver co-investigators to further refine TEACH and create a telehealth adaptation.

For the current trial, TEACH will consist of six live one-hour HIPAA-compliant telehealth (Zoom) video sessions administered weekly (versus in person) with caregiver/partner support (see Table 1). During each session, an interventionist will teach new skills, assess home practice, answer questions, and help identify how participants will use the skills in their daily lives. Based on the refinement of TEACH, supplemental tools/practice activities will also be available to participants (via REDCap), and use of these tools will be tracked by the interventionist/research team. Licensed mental health providers and/or doctoral students under supervision in the US and Canada will serve as the interventionists. Every effort will be made to deliver TEACH consistently; however, in the case of technical difficulties or other access issues, interventionists will deliver TEACH using alternative strategies (e.g., phone call).

**Table 1 Tab1:** TEACH protocol

Session	Attendee(s)	Adolescent Content	Young Adult Content
1	Participant, caregiver	Psychoeducation Caregiver guidelines	
2	Participant	Activity Pacing	
		Deep breathing Sleep hygiene	Pleasant activities Communication

### Interventionist training

Interventionists will receive individual training from the PI ([name]) or other trained interventionists either in person or via Zoom conference. The protocol will be reviewed and practiced by interventionists, with direct feedback provided during training. Continued feedback/monitoring will be provided throughout. Interventionists will meet periodically via Zoom to discuss barriers and tips learned to ensure best practices.

#### Treatment fidelity

All sessions will be video-recorded and stored. Each primary site will have trained independent staff members who will complete an integrity rating for each session. The rating consists of a checklist to ensure consistent treatment content across all participants by the interventionist. Monthly interventionist meetings will be held to ensure consistency among treatment at US and Canada sites.

### Medical TAU

All participants across both conditions will continue standard medical treatment by their pediatric rheumatology team (TAU), either alone or in combination with TEACH.

### Data management and handling of missing data

Data will be managed and stored using REDCap, a secure software designed exclusively to support data capture for research studies. Considerable efforts (e.g., electronic data capture, standardized data checking strategies) will be made to limit missing data. Rates of missing data will be reported and addressed statistically if over 10%. If missing data are considered to be missing at random, multiple imputation or inverse probability weighting will be implemented at the time of final analysis. Given the modest sample size of this study, every effort will be made to minimize missing data.

### Statistical analysis plan

Recruitment/retention rates and qualitative analysis of the semi-structured interview will assess feasibility, tolerability, and acceptability of TEACH. Evidence of feasibility is demonstrated by > 65% of patients/families approached will agree to participate (H1) and > 80% of recruits will complete the TEACH protocol (H2). Participant feedback about TEACH will be solicited and will support program feasibility (H3). Recorded qualitative interviews will be transcribed for the team to identify and code themes and key content domains. Discrepancies between reviewers will be discussed at length until a consensus is reached. Members of the research team ([name], [name]) are experts in qualitative data analysis [18, 44–48].

A repeated measures ANOVA will evaluate the hypotheses outlined in Aim 2. Participants will be allocated to the TEACH + TAU or TAU group. The mean change in fatigue (main secondary outcome), depressive symptoms, and pain from baseline to eight-week post will be analyzed separately to determine the effect of TEACH on these symptoms in comparison to the control group.

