### Randomization and blinding

Eligible participants will be randomized to receive either TEACH + TAU or TAU alone in this open trial. Randomization scheduling will be computer-generated by a biostatistician at MSU and stratified based on the two main study sites and two age groups (< 18, 18 +), with a 1:1 ratio for each condition. We will also use blocking to keep the ratio of TEACH + TAU vs. TAU approximately equal throughout the trial. The study team including the site recruiters will be masked to the block size(s). Post assessment and follow up measures will be collected autonomously using online methods, allowing for blinded collection of outcome data irrespective of group assignment.

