#### Sample Size Estimate

The sample size estimate for this was based on a two-sided test for the averaged difference between two group means (for fatigue) using a repeated measures ANOVA design with a significance level of *p* < 0.05. A minimum sample size of 60 participants (30 per treatment group) and an effect size of 0.6 [18] results in 76% power. Given that an estimated 80% of participants will be retained in the study, a total of 75 participants will need enroll in the study.

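### Testing change scores by repeated measures ANOVA is valid but less efficient than baseline-adjusted ANCOVA for the three symptom outcomes

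*Protocol article*

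**What the plan says.** The Statistical analysis plan section of the protocol article names the efficacy method: "A repeated measures ANOVA will evaluate the hypotheses outlined in Aim 2". The quantity is the mean change in fatigue, depressive symptoms and pain, which "from baseline to eight-week post will be analyzed separately to determine the effect of TEACH on these symptoms in comparison to the control group". Fatigue is the main secondary outcome. No covariate is named, and none is excluded.

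Under Randomization and blinding, allocation is "stratified based on the two main study sites and two age groups (< 18, 18 +), with a 1:1 ratio for each condition".

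The Sample Size Estimate section describes a "two-sided test for the averaged difference between two group means (for fatigue) using a repeated measures ANOVA design". It gives 60 completers, 30 per group, and says that "an effect size of 0.6 [18] results in 76% power". It states no correlation between visits and does not say which SD the 0.6 is measured in.

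**The concern.** The article settles the form of the efficacy comparison, and the form is change from baseline. In a randomised trial that is rarely the most precise use of a baseline measurement. Subtracting baseline assumes that a participant one point higher at entry will be one point higher at week 8. When the true slope is below 1, the subtraction adds noise. ANCOVA estimates the slope from the data.

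What is at stake is precision. With about 60 completers, the choice decides how wide the intervals are for fatigue, depressive symptoms and pain. It also decides how useful the effect estimate is for the larger study that the Discussion foresees.

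**Working it through.** **Inputs.** From Sample Size Estimate: 30 per arm analysed, two-sided alpha 0.05, effect size 0.6, stated power 76%. Not given: rho and the SD unit of the 0.6. Below, rho runs from 0.3 to 0.8, and 0.6 is first taken in SD units of the raw score.

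**The plan's own figures.** Enrolment: 60/0.80 = 75, as stated. Power: for an average of two measurements the SD factor is sqrt((1+rho)/2). At an assumed rho of 0.5 this is sqrt(0.75) = 0.866, the noncentrality is 0.6 × sqrt(30/2)/0.866 = 2.683, and power is 76.5% (normal) or 75.1% (t). This route is not unique. A change-score test has factor sqrt(2(1−rho)), which is also 0.866 at rho = 0.625 and gives the same power. An average of three measurements at rho 0.6 gives 77.5% or 76.1%. So 76% is attainable, but it does not reveal which contrast or correlation was used.

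**Equivalence.** With two visits and two groups, the group-by-time term compares mean (week 8 − baseline) between arms. That is the two-sample t-test on change, with 58 df.

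**Variances per participant**, with SDs sx (baseline) and sy (week 8):
- change: sx² + sy² − 2·rho·sx·sy
- ANCOVA: sy²(1 − rho²)
- change minus ANCOVA: (sx − rho·sy)², never negative and zero only when the slope rho·sy/sx equals 1.

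With equal SDs the two are 2(1−rho) and (1−rho²) times the common variance, so ANCOVA/change = (1+rho)/2.

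**Power**, noncentrality = 0.6 × sqrt(15)/k = 2.324/k, with k = sqrt(2(1−rho)) for change (58 df) and k = sqrt(1−rho²) for ANCOVA with baseline and all four strata (54 df):

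| rho | noncentrality, change | noncentrality, ANCOVA | power, change | power, ANCOVA | variance ratio | completers giving equal precision (60 × ratio) |
|---|---|---|---|---|---|---|
| 0.3 | 1.964 | 2.436 | 48.9% | 66.7% | 0.65 | 39 |
| 0.5 | 2.324 | 2.683 | 62.8% | 75.0% | 0.75 | 45 |
| 0.7 | 3.000 | 3.254 | 83.9% | 89.2% | 0.85 | 51 |
| 0.8 | 3.674 | 3.873 | 95.1% | 96.7% | 0.90 | 54 |

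The interval width shrinks by 1 − sqrt((1+rho)/2): about 19%, 13%, 8% and 5%.

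**If 0.6 is in SD units of change instead**, the change test has 62.8% power throughout, and ANCOVA has 80.8%, 75.0%, 69.7% and 67.2% at the same four values of rho.

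**Strata terms.** Going from 57 to 54 df costs about 0.1 percentage point of power. In simulation (60 participants, stratified allocation, 6,000 runs per setting), site and age each shifted both visits by 0.5 SD. Adding the strata to ANCOVA then gained about 0 to 2 points, and the change test without strata rejected a true null 4.6% to 5.1% of the time.

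A different picture needs strata that predict change. Suppose age shifts week 8 only, by g SD, with half the sample in each age group and rho 0.5. The within-stratum change variance is 1, and the pooled variance becomes 1 + g²/4, that is 1.0625 at g = 0.5 and 1.16 at g = 0.8. Type I error of the change test is then about 4.4% and 3.5%, which is conservative.

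**The case against.** Change-score ANOVA is conventional, unbiased under randomisation and has the right type I error. It also belongs to the same family as the method named for sizing. All of that stands. The gain is modest if rho is high, and smaller still if the entry thresholds make the baseline SD smaller than the week-8 SD, because the true slope then moves towards 1. Efficacy is secondary to feasibility here. That limits how much weight the point carries, but gives no reason to prefer the less precise estimator.

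Four stronger readings are tempting and are not supported.
- *The analysis throws baseline away.* It does not: it uses baseline with a fixed slope of 1.
- *The analysis ignores the strata.* The article is silent on covariates. A repeated measures ANOVA can carry site and age as between-subject factors, and a condensed article may leave that to the full plan.
- *Standard errors are too large because the strata are prognostic.* A stable site or age difference cancels in a change score. Standard errors are inflated only if the strata predict change, which the article does not show.
- *True power is 63%, not 76%.* That figure needs rho 0.5. At rho 0.625 the change test reproduces the stated power, and the article does not say which value was assumed.

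**Conclusion.** The point holds as an efficiency improvement. The stated test is valid, but in large samples baseline-adjusted ANCOVA is never less precise, and it is more precise unless the true slope on baseline is 1. With equal variances, raw-score SD units and 30 per arm, the gain is about 18 percentage points of power at rho 0.3, 12 at 0.5, 5 at 0.7 and under 2 at 0.8. These sizes rest on an assumed rho and SD unit. Nearly all of the gain comes from the baseline covariate. The strata terms align the analysis with the design at negligible cost. Nothing here invalidates the trial or its primary feasibility aim; the change is worth making before the data are analysed.

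**What to change.** Replace the efficacy sentence with this: for each of fatigue, depressive symptoms and pain, the week-8 difference between arms will be estimated by ANCOVA (or a constrained longitudinal mixed model) with treatment, the baseline value of that outcome, main site (US or Canada) and age group (under 18, or 18 and over), and reported as an adjusted difference with a 95% confidence interval.

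Age group has a second claim to a place in the model, because it decides which fatigue and depression instrument a participant completes. If the full plan already lists these covariates, the article needs only to say so. It would also help to state, in the sample size paragraph, the correlation assumed and the SD in which the 0.6 is expressed.

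Cost: one sentence, no new data, one degree of freedom for baseline and two or three for the strata. It should be fixed before outcome data by arm are seen, so that the choice of covariates cannot depend on the result.

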#### Exploratory Outcomes 

Given that data from exploratory variables will be collected throughout the study, additional investigations into the effect of TEACH on these variables will be conducted. Long-term outcomes measured at the 20-week assessment of TEACH will be evaluated.

#### Sample Size Estimate

The sample size estimate for this was based on a two-sided test for the averaged difference between two group means (for fatigue) using a repeated measures ANOVA design with a significance level of *p* < 0.05. A minimum sample size of 60 participants (30 per treatment group) and an effect size of 0.6 [18] results in 76% power. Given that an estimated 80% of participants will be retained in the study, a total of 75 participants will need enroll in the study.

## Discussion

cSLE is a chronic, debilitating autoimmune disease associated with more severe symptoms as compared to adult-onset SLE and a 20-fold increased risk of mortality [49]. cSLE is commonly associated with fatigue, mood issues, and pain, which contribute to poor health-related quality of life [2, 3]. Given these common symptoms are modifiable with nonpharmacological therapies, CBT may optimize patient outcomes as part of a multi-disciplinary approach to care [50]; however, there is mixed evidence to date that CBT manages mood and related symptoms in children [18, 51] and adults [13] with SLE. A tailored intervention such as TEACH using evidence-based cognitive behavioral and mindfulness meditation techniques to manage fatigue, depressive symptoms and pain may be needed to address concerns specific to this population.

While we have demonstrated feasibility of TEACH in a pilot investigation [18], a rigorous and well-controlled trial of this promising approach is critically needed to advance understanding and improve outcomes for youth with cSLE. TEACH is a brief tailored therapy designed to improve fatigue, mood, and pain in youth with cSLE. It is important to assess if TEACH is feasible and associated with improvements in these symptoms following treatment as compared to standard medical care. Once these effects are established, we will investigate additional factors such as patterns/predictors of treatment response.

COVID-19 impacted the study planning and recruitment plan. As such, COVID-related distress will now be measured and targeted. Furthermore, we expect enrollment rates to vary during different periods of the COVID-19 pandemic. We will examine these data carefully in the context of when it was collected.

We anticipate minimal risk and maximal benefits to patients/families. The present trial allows for understanding of treatment effects. Lack of active treatment comparator and a modest sample size are limitations. In the future, we plan to test the *implementation* of TEACH in a larger scale multi-site investigation and assess sustainability of treatment effects. Assuming TEACH is effective and future implementation efforts are successful, we will share the program with rheumatology providers to integrate TEACH into routine care. Future work will also examine mechanisms of treatment response and whether modifications (e.g., booster sessions) are needed.

## Conclusion

In conclusion, this is the first RCT of a remotely delivered, tailored psychological treatment to target fatigue, mood symptoms, and pain in youth with cSLE. If successful, TEACH has the potential to positively impact the standard of care of youth with cSLE.

## Data Availability

Not applicable.

## Abbreviations

ACEs: Adverse Childhood Experiences
BDI-II: Beck Depression Inventory-II
CAN: Canada
CARRA: Childhood Arthritis and Rheumatology Research Alliance
CARRA-AF: Childhood Arthritis and Rheumatology Research Alliance – Arthritis Foundation
CBT: Cognitive Behavioral Therapy
CDI-II: Children’s Depression Inventory 2nd Edition
cSLE: Childhood-onset Systemic Lupus Erythematosus
DASS-21: Depression Anxiety Stress Scales-21
MASRI: Medication Adherence Self-Report Inventory
MSU: Michigan State University
RCT: Randomized controlled trial
SCARED: Screen for Child Anxiety Related Disorders
SDI: Systemic Lupus International Collaborating Clinics Damage Index
SLEDAI-2K: Systemic Lupus Erythematosus Disease Activity Index 2000
TAU: Treatment as usual
TEACH: Treatment and Education Approach for CHildhood-onset Lupus
US: United States
VAS: Visual Analog Scale
